## Abstract

Background: Approximately 11.3% of the US population has diabetes. The burden of diabetes is higher in older adults and African Americans (AAs), such that 40% of adults aged 50 years and older have diabetes; African Americans are 60% more likely to be diagnosed with diabetes compared to non-Hispanic Whites (NHWs). Structural racism has resulted in fewer economic and educational opportunities for AAs, higher social risks, and unmet basic needs, which result in financial instability, housing instability, food insecurity, and a lack of transportation compared to NHWs. The presence of these unmet basic needs is a driver of poor adherence to diabetes self-management in older AAs. Aim: To test the preliminary efficacy of a nurse case-manager, telephone-delivered intervention that provides foundational diabetes self-management education and skills training, while also addressing and resolving the unmet social needs of older AAs with poorly controlled type 2 diabetes mellitus (T2DM). The primary hypothesis is that older AAs with T2DM randomized to the DM Social Needs intervention will have significantly lower hemoglobin A1C (HbA1C), blood pressure, and LDL levels compared to the usual care arm at 6 months post randomization. Methods: This is a three-year prospective, randomized clinical trial that will enroll 100 AAs aged 50 and older with type 2 diabetes (T2DM) and HbA1C ≥ 8% into one of the following two groups: (1) a nurse case-manager, telephone-delivered intervention that provides foundational diabetes self-management education and skills training, but also addresses and resolves unmet social needs; or (2) an enhanced usual care group that will receive mailed diabetes education materials. Participants will be followed for 6 months to determine the effect of the intervention on HbA1C, blood pressure, and low-density lipoprotein (LDL) cholesterol levels. Results: Baseline characteristics will be presented by study group, and within- and between-group changes in primary outcomes from baseline to 6 months will be reported. Conclusion: The results from this study will provide insights into the efficacy of a combined diabetes education and skills training and social needs resolution intervention for older African Americans with poorly controlled type 2 diabetes and will inform strategies to improve diabetes outcomes for this vulnerable population.

## 1. Introduction

Approximately 11.3% of the US population has diabetes and the annual cost of diabetes is about USD 327 billion [1]. More than 50% of the lifetime medical cost of diabetes is due to diabetes-related complications [2]. Individuals with diabetes are twice as likely to have microvascular (retinopathy, nephropathy, and neuropathy) and macrovascular (coronary heart disease, cerebrovascular disease, and peripheral vascular disease) complications compared to those without diabetes [3,4,5,6]. The burden of diabetes is higher in older adults, such that 40% of adults aged 50 years and older have diabetes, over 60% of diabetes costs are attributed to Medicare and Medicaid, and older adults experience more complications compared to younger adults [4,7,8]. As the US population continues to age, the prevalence of diabetes will continue to rise in older adults [8,9,10,11]. 

The prevalence of diabetes is higher in African Americans (AAs) and they are 60% more likely to be diagnosed with diabetes compared to non-Hispanic Whites (NHWs) [12]. On average, AAs are diagnosed with diabetes at a younger age [13], are more likely to experience complications, are four times more likely to have an amputation, and are twice as likely to die as a result of diabetes compared to NHWs [12,13,14,15,16]. The higher rate of complications in AAs is due to the less optimal control of hemoglobin A1C (HbA1C), blood pressure, and low-density lipoprotein (LDL) levels compared to NHWs [12,13,14,15,16,17]. Although optimal diabetes control can be achieved by adherence to diabetes self-management guidelines including medication adherence, blood glucose self-monitoring, attending doctor’s visits, healthy diet, and exercise, AAs are less adherent to diabetes self-management guidelines compared to NHWs [18].

Structural racism and the reinforcement of inequitable systems over time has resulted in fewer economic and educational opportunities for AAs, higher social risks, and unmet basic needs, resulting in financial instability, housing instability, food insecurity, and lack of transportation compared to NHWs [16,19]. For example, the proportion of older AAs living in poverty is higher than that of NHWs (19% vs. 7%); food and housing insecurity levels are higher in AAs compared to NHWs (44% vs. 22%); and AAs have eight times less wealth compared to NHWs [20,21,22,23,24]. The presence of these unmet basic needs is a driver of poor adherence to diabetes self-management in older AAs, including medication adherence, glucose self-monitoring, healthy eating, completing medical visits, and purchasing necessary diabetes care supplies [18,25,26,27,28]. 

However, there is evidence that basic needs referral is not sufficient to address unmet social needs [29]; therefore, to achieve optimal outcomes for older AAs with type 2 diabetes mellitus (T2DM) and unmet social needs, it is imperative to combine traditional diabetes education and skills training with strategies to identify and resolve unmet social needs. Therefore, to address this gap in knowledge, we will use a randomized controlled trial design to test the preliminary efficacy of a combined diabetes education/skills training and social needs resolution (DM Social Needs) intervention on improving clinical outcomes for older AAs with T2DM. The principal investigator (PI) ([name]) and research team are well suited to complete this study. The team has been successful in previously recruiting, enrolling, and completing clinical trials with older African American patients with poorly controlled type 2 diabetes [30,31,32,33,34]. 

### Study Aims and Objectives

The primary aim of this study is to test the preliminary efficacy of the DM Social Needs intervention on clinical outcomes (HbA1C, blood pressure, and LDL levels) in older AAs with uncontrolled T2DM. The secondary aim is to test the preliminary efficacy of the DM Social Needs intervention on patient-reported outcomes (based on PROMIS measures) in older AAs with uncontrolled T2DM. The primary outcome is HbA1C at 6 months post randomization, the secondary outcome is blood pressure at 6 months post randomization, and the tertiary outcomes are LDL and patient-reported outcomes of global health, fatigue, pain interference, and social participation at 6 months post randomization. 

## 2. Methods

This three-year randomized clinical trial will test the efficacy of the six-session nurse case-manager, telephone-delivered combined diabetes education/skills training and social needs resolution (DM Social Needs) intervention on improving clinical outcomes for AAs aged 50 and older with poorly controlled type 2 diabetes (HbA1C ≥ 8%). Funding was awarded in November 2022 and has an anticipated end date of November 2025. One-to-one individual-level randomization will be used to assign eligible participants to study groups. Outcome assessments will occur at baseline, 3 months, and 6 months post randomization.

### 2.1. Ethics and Trial Registration

This study is funded by a grant from the American Diabetes Association (ADA) (11-22-JDFHD-01; PI: [name]). The trial and study protocol were approved by the Medical College of Wisconsin Institutional Review Board on 24 May 2023 (PRO00046456). The trial was registered on ClinicalTrials.gov (trial number: NCT05935410) on 27 June 2023. 

### 2.2. Trial Status

This study was funded in November 2022 and was assigned protocol number PRO00046456. As of September 2024, 53 of the 100 total participants have been randomized. Recruitment is expected to be completed by May 2025.

### 2.3. Trial Population and Recruitment

A total of 100 AAs aged 50 and older with poorly controlled T2DM (HbA1C ≥ 8%) will be randomized in a 1:1 ratio into one of two study groups—(1) nurse-led, telephone-delivered DM Social Needs intervention that includes education and skills training on diabetes management and problem solving and the resolution of social needs during monthly, 60 minute phone calls (*n* = 50); and (2) an enhanced usual care group that will receive mailed diabetes education materials each month for 6 months in accordance with recommendations from the ADA (*n* = 50). Participants will be followed for 6 months to evaluate the preliminary efficacy of the intervention on clinical outcomes (HbA1C, blood pressure, and LDL levels) and patient-reported outcomes (PROs).

A multifaceted approach will be used to recruit AA older adults with poorly controlled T2DM after receiving approval from the Institutional Review Board (IRB). (1) Housing Authorities. The study PI will meet with housing authority leadership for public and senior housing communities to obtain approval to recruit and share information about the study at their locations. (2) Community Leaders. The study PI will meet with other community leaders including church/religious leaders, small business owners, and federally qualified health center and community center leaders to obtain approval to recruit and share information about the study at their locations. (3) Mailing Lists. Targeted mailing lists obtained from electronic health records and other publicly available sources will be used to send letters describing the study and providing instructions on how to contact the research team will be sent to older African Americans in an effort to reach eligible patients. (4) Referrals. Referrals will be accepted from healthcare providers, community members, or other study participants. Individuals who are referred to participate will be contacted by the research team to assess interest, willingness, and eligibility to participate.

Individuals who are interested in participating will be scheduled for screening. Research staff will obtain signed informed consent prior to initiating study procedures for all participants. Study eligibility criteria are as follows: Inclusion: (1) age 50 and older; (2) self-identified as AA or Black; (3) self-reported diagnosis of T2DM; (4) HbA1C ≥ 8% at the screening visit. Exclusion: (1) self-reported participation in other diabetes clinical trials; (2) alcohol or drug abuse or dependency, as assessed by the CAGE-AID; (3) mental confusion at screening assessment, suggesting significant dementia; (4) life expectancy < 6 months. All treatments including insulin, oral medications, both, or neither were acceptable for the study, and eligible participants were enrolled regardless of treatment. 

### 2.4. Randomization

A permuted block randomization method will be used to assign patients to control or intervention. Block size will be varied to minimize the likelihood that the blind will be broken. The randomization will be computer generated and stratified by screening HbA1C levels (8–10% vs. >10%). Study staff responsible for completing surveys and collecting measures at baseline, 3 months, and 6 months post randomization will be blinded to study group assignment. 

### 2.5. Combined Diabetes Education/Skills Training and Social Needs Resolution (DM Social Needs) Intervention

The proposed outline of the six-session nurse-led, telephone-delivered DM Social Needs intervention includes education and skills training on diabetes management, problem solving, and resolution of social needs during monthly, 60 minute phone calls. Intervention sessions will be delivered by trained nurse case-managers using diabetes education and skills training materials in accordance with ADA recommendations and guidelines. The baseline session will include an intake using the accountable care organization social determinants of health screening tool [35] to identify and prioritize the patient’s top three social needs to resolve during the six-month study. Diabetes education and skills training topics will be discussed monthly and include an overview of diabetes; blood glucose monitoring; medication adherence; diet; exercise; blood pressure; cholesterol; and foot, skin, and dental care. Prioritized social needs will be addressed using existing community-based social services in order to resolve prioritized needs. 

### 2.6. Enhanced Usual Care Group

Participants in the usual care arm will receive mailed diabetes education materials in accordance with recommendations from the American Diabetes Association (ADA) monthly [36]. Diabetes education material will be based on ADA education documents that are publicly available and will cover the following topics: (1) overview of diabetes; (2) self-monitoring of blood glucose; (3) medication adherence; (4) basics of eating and exercise; (5) blood pressure and cholesterol; and (6) foot, skin, and dental care.

### 2.7. Study Instruments and Data Collection Schedule

Figure 1 is a flow diagram of the study design and visit schedule. Table 1 shows the data collection schedule, and Table 2 provides a description of the measures and scales used to collect data. 

### 2.8. Primary Outcomes

The three primary outcomes for this study are HbA1C, blood pressure, and low-density lipoprotein cholesterol levels. Primary outcomes will be collected at baseline, 3 months, and 6 months post randomization. 

### 2.9. Data Management

Research Electronic Data Capture (REDCap) is a secure, web-based application that will be used for data management. The PI will monitor data quality and integrity and will meet with co-investigators and the study team weekly to discuss recruitment, retention, and data entry. 

### 2.10. Sample Size and Power

Clinical outcomes (HbA1C, blood pressure, and LDL levels) and patient-reported outcomes (based on PROMIS measures) will be assessed at baseline, 3 months, and 6 months post randomization with the primary time point being at 6 months post randomization. Assuming two post randomization measurement time points, with a level of significance α = 0.10, and given that this is a pilot study [48], two-tailed comparison, the correlation between pairs of repeated measurements within participants (interclass correlation) no larger than ρ = 0.5, with an AR (1) covariance structure, we estimate that 40 patients per intervention group are needed to detect, with 80% power, a standardized effect size of 0.3 sd (Cohen’s d) for the quantitative outcomes for Aims 1–2. For example, for the outcomes HbA1C, systolic blood pressure, and LDL, assuming standard deviations (sds) of 1.9 percentage points, 19.9 mmHg, and 20 mg/DL, respectively, the corresponding raw effect sizes that can be detected between the intervention and control group are 0.57 percentage points, 6.0 mmHg, and 6.0 mg/DL, respectively. Intervention sample sizes of 40 patients per intervention group will produce 90% confidence interval (CI) estimates of effect sizes (differences in intervention means) with a precision of ±0.26 sds for study outcomes. To account for the missing information in the intent-to-treat (ITT) sample and the dilution effect of ITT analyses, we will increase the sample size by 20% to achieve a final ITT sample size of 50 patients randomized to each treatment group. Because the objective is to obtain preliminary evidence of efficacy rather than to definitively confirm/refute hypotheses, we have used less stringent criteria for power, level of significance, and confidence interval estimates (i.e., power = 0.8, alpha = 0.1, and 90%CI) than for a subsequent confirmatory randomized controlled trial (RCT). 

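### Section 2.10: 40 per group does not give 80% power for 0.3 sd; power is about 40-46% for the planned 6-month contrast and at most about 60% on the most favourable reading

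*Protocol article*

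**What the plan says.** All the design figures are in section 2.10 of the protocol article.

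- Test: "with a level of significance α = 0.10", as a "two-tailed comparison".
- Repeated measures: two post-randomization visits, within-participant correlation of at most 0.5, AR(1) covariance, primary time point 6 months.
- Power claim: "we estimate that 40 patients per intervention group are needed to detect, with 80% power, a standardized effect size of 0.3 sd".
- Raw units: "assuming standard deviations (sds) of 1.9 percentage points, 19.9 mmHg, and 20 mg/DL" for HbA1C, systolic blood pressure and LDL. From these, "the corresponding raw effect sizes that can be detected between the intervention and control group are 0.57 percentage points", with 6.0 mmHg and 6.0 mg/dL for the other two.
- Precision: 40 per group should yield 90% confidence intervals "with a precision of ±0.26 sds for study outcomes".
- Inflation: the plan will "increase the sample size by 20% to achieve a final ITT sample size of 50 patients" per arm.

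Section 2.11 fixes the analysis: a longitudinal model with treatment, time, their interaction and the baseline value of the outcome as covariate. The arms are compared at 6 months with a 90% confidence interval and p-value.

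**The concern.** The power claim and the precision claim stand in one paragraph, for the same group size and the same 10% two-sided error level. Each fixes a standard error, and the two standard errors differ. The contrast in section 2.11 is less precise than either.

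At stake is how the result will be read. The article presents effects of 0.57 points, 6.0 mmHg and 6.0 mg/dL as detectable with 80% power, and the Discussion says the results will support a proposal for a larger trial. A non-significant result judged against a claimed 80% could pass for evidence that effects of that size are absent, and so discourage or mis-size the next study.

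**Working it through.** **Inputs.** From section 2.10: two-sided alpha 0.10 (z = 1.645), power 80% (z = 0.842), n = 40 per arm, effect 0.3 sd, correlation rho up to 0.5, AR(1), two post-randomization visits. From section 2.11: baseline as covariate, contrast at 6 months.

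**Formulas.** In sd units, with k the variance factor of the contrast:

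- SE = √(2k/n)
- power at 0.3 sd = Φ(0.3/SE − 1.645)
- 80%-power effect = (1.645 + 0.842) × SE = 2.486 × SE (from unrounded quantiles)
- 90% CI half-width = 1.645 × SE

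**Step 1: the plan's own figures.** The raw effects are 0.3 × sd: 0.3 × 1.9 = 0.57; 0.3 × 19.9 = 5.97; 0.3 × 20 = 6.0. So the sds are plain outcome sds, and this conversion is consistent. The precision is reproduced with k = 0.5: SE = √(2 × 0.5/40) = 0.158, and 1.645 × 0.158 = 0.26. The 80% power is not reproduced.

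**Step 2: precision against power, with no choice of model.**

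- ±0.26 sd gives SE = 0.26/1.645 = 0.158. Power at 0.3 sd = Φ(0.3/0.158 − 1.645) = Φ(0.25) = 60%. The 80%-power effect = 2.486 × 0.158 = 0.39 sd.
- Conversely, 80% power at 0.3 sd needs SE = 0.3/2.486 = 0.121, a half-width of ±0.20 sd.

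The two statements cannot both be true.

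**Step 3: variance factors.**

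- 6-month difference adjusted for baseline: k = 1 − r², with r the baseline-to-6-month correlation. AR(1) with rho = 0.5 gives r = 0.5² = 0.25 and k = 0.9375. If r itself is 0.5, k = 0.75.
- Average of the two visits, unadjusted: k = (1 + rho)/2, which is 0.75 at rho = 0.5 and 0.50 at rho = 0.
- Average of the two visits, baseline-adjusted, rho = 0.5: AR(1) gives k = 0.75 − 0.375² = 0.609; compound symmetry gives k = 0.75 − 0.5² = 0.50.

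| Contrast, n = 40 per arm | k | SE | 90% CI | Power at 0.3 sd | 80%-power effect |
|---|---|---|---|---|---|
| 6 months, adjusted, AR(1), r = 0.25 | 0.9375 | 0.217 | ±0.36 | 40% | 0.538 sd |
| 6 months, adjusted, r = 0.5 | 0.75 | 0.194 | ±0.32 | 46% | 0.482 sd |
| Average of visits, adjusted, AR(1) | 0.609 | 0.175 | ±0.29 | 53% | 0.434 sd |
| Best case for rho up to 0.5 | 0.50 | 0.158 | ±0.26 | 60% | 0.393 sd |

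Noncentral t instead of normal quantiles lowers these powers by less than one percentage point.

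**Step 4: what 80% would require.** k = n × SE²/2 = 40 × 0.121²/2 = 0.291. For the adjusted 6-month contrast this means r = √(1 − 0.291) = 0.84, against a stated maximum of 0.5. At the plan's correlations, n = 2k × (2.486/0.3)² gives 104 (r = 0.5) to 129 (r = 0.25) analysed per arm.

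**Step 5: raw units for the planned contrast (0.482 to 0.538 sd).**

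- HbA1C: 0.482 × 1.9 = 0.92 to 0.538 × 1.9 = 1.02 points (stated 0.57).
- Systolic blood pressure: 0.482 × 19.9 = 9.6 to 0.538 × 19.9 = 10.7 mmHg (stated 6.0).
- LDL: 0.482 × 20 = 9.6 to 0.538 × 20 = 10.8 mg/dL (stated 6.0).

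**Step 6: all 50 per arm analysed.** For r = 0.25, SE = √(2 × 0.9375/50) = 0.194 and power is 46%. For r = 0.5, SE = √(2 × 0.75/50) = 0.173 and power is 54% (0.535). The best case, k = 0.50, gives 68%.

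**The case against.** The strongest defence is that this is a pilot that seeks preliminary evidence, reports 90% intervals, lists its small sample as a limitation and leaves the efficacy question to a larger trial. That lowers the consequences of the error. It does not explain the figure: the pilot allowance consists of alpha 0.10 and the 90% interval, both are already in the calculation, and the section still claims power of 0.8.

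Repeated measurement helps, but with correlations up to 0.5 it takes power no higher than 60%. A one-sided test at 0.10 would give at most 73% with 40 per arm, and the section says two-tailed.

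Three stronger readings are tempting and are not supported:

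- That 40-46% is all the stated inputs can give. It is the range for the planned contrast. Averaging both visits with baseline adjustment gives 53-60%, and the printed ±0.26 sd matches the 60% case. The 46% end also takes the baseline-to-6-month correlation as 0.5, where the stated AR(1) makes it 0.25.
- That the trial would miss an effect of 0.3 sd more often than find it. This fails on some readings: power is 54% with 50 per arm at r = 0.5. Forty is a planning figure, and the longitudinal model also draws on participants who have only a 3-month value.
- That the step from 40 to 50 is used up by 20% missing data and leaves nothing for dilution. 40/0.8 = 50 is sound arithmetic, but section 2.10 states no loss rate and makes one allowance for missing information and dilution together. How it divides cannot be known.

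On the correlation bound, the defence is partly right. For an unadjusted average of the two visits, an upper limit on rho is the cautious choice. It stops being so for the baseline-adjusted 6-month contrast, where a smaller correlation worsens precision. This is a mismatch between sections 2.10 and 2.11, not a separate error.

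**Conclusion.** The concern holds. The stated 80% power for 0.3 sd, and the raw detectable effects built on it, are wrong on the plan's own inputs. The contradiction with the ±0.26 sd precision needs no modelling assumption: that figure means 60% power and a detectable effect of 0.39 sd.

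For the contrast that section 2.11 will test, power at 0.3 sd is 40-46% with 40 analysed per arm and 46-54% with all 50. The effect detectable with 80% power at 40 per arm is 0.48-0.54 sd, which is 1.6 to 1.8 times the stated 0.3 (0.482/0.3 and 0.538/0.3). These ranges assume equal variances over time, the stated sds and a baseline-to-6-month correlation between 0.25 and 0.5. A true correlation near 0.84 would restore the claim, but it lies outside what the section assumes.

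The sample size itself is not shown to be unsuitable for a pilot. What is wrong is the stated capability, and it should be corrected before results are interpreted.

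**What to change.** Keep 100 participants and revise section 2.10:

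1. State power, detectable effects and precision for the baseline-adjusted 6-month difference. At 40 analysed per arm: about 40-46% power for 0.3 sd; 80% power for about 0.48-0.54 sd (HbA1C about 0.9-1.0 points, systolic blood pressure about 10 mmHg, LDL about 10 mg/dL); 90% CI about ±0.32 to ±0.36 sd. Add that power at 0.3 sd is about 46-54% if all 50 per arm are analysed.
2. Note that the most favourable reading at 40 per arm gives at most about 60% power for 0.3 sd.
3. Replace the upper bound on the correlation with an assumed baseline-to-6-month correlation and a range, and show the figures over that range.

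The sentence on inflation from 40 to 50 needs no change on this account.

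The cost is a recalculation and new wording in one section. The stated figures become less favourable. Recruitment, design and analysis stay as they are, and since the article reports 53 of 100 randomized as of September 2024 and plans analysis only after follow-up ends, the change can be made before any result is read against the old claim.

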### 2.11. Data Analysis

The intent-to-treat (ITT) sample comprises all randomized participants. Univariate descriptive statistics and frequency distributions will be calculated for clinical and other baseline covariates for the total sample to describe the study population, and by intervention group to assess the similarity of the treatment arms at baseline to confirm randomization success and to identify potential confounding variables to be used as covariates in secondary analyses. We will use a longitudinal general linear model approach as the analytic framework for inferential analyses. This method allows for missing data under the assumption of missing at random (MAR), accounts for the correlated longitudinal measurements within subjects, and accommodates a wide range of distributional assumptions through the specification of appropriate link functions. For the primary analyses of patient clinical outcomes (HbA1C, blood pressure, and lipid levels) and patient-reported outcomes, the identify link function will be used to compare 6 month treatment means and longitudinal trajectories for the DM Social Needs and usual care arms. Each outcome within each domain will be used separately as the dependent variable in the models with intervention, time, and time-by-intervention as the primary independent variables and baseline score for a given outcome variable as an adjustment covariable. In further secondary analyses, covariates (e.g., sociodemographics, health literacy, and comorbidities) will be added to each model to adjust for confounding variables, if indicated. Model-generated least squares intervention means, and the intervention mean difference (effect size), for clinical and patient-reported outcomes will be estimated, and intervention differences will be compared for significance at the primary endpoint (6 month) using 90% confidence intervals and *p*-values for appropriate model-derived contrasts. 

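### The stated 90% CI precision of ±0.26 sd at 40 per arm cannot be reached for the 6-month between-arm difference under the plan's own correlation assumption; about ±0.32 to ±0.37 sd is

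*Protocol article*

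**What the plan says.** Section 2.10 (Sample Size and Power) gives these planning inputs:

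- Visits: "Assuming two post randomization measurement time points", with 6 months as the primary time point
- Error rate: "with a level of significance α = 0.10" and a "two-tailed comparison"
- Dependence within a person: "the correlation between pairs of repeated measurements within participants (interclass correlation) no larger than ρ = 0.5"
- Covariance pattern: "with an AR (1) covariance structure"

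From these it claims 80% power at 0.3 sd with 40 per group. It then turns to precision. The basis given is "Intervention sample sizes of 40 patients per intervention group", and the claim made for them is that they "will produce 90% confidence interval (CI) estimates of effect sizes (differences in intervention means) with a precision of ±0.26 sds for study outcomes". The number randomized is raised to 50 per group to allow for missing information and dilution under intention to treat.

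Section 2.11 (Data Analysis) specifies a longitudinal model with intervention, time and their interaction, and the outcome's own baseline value as a covariate. It states that "intervention differences will be compared for significance at the primary endpoint (6 month) using 90% confidence intervals". Neither section says that the treatment effect will be averaged over the 3- and 6-month visits.

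**The concern.** The precision sentence describes a difference between arms, and the only difference the plan commits to judging is the one at 6 months. For a single visit with 40 per arm, ±0.26 sd looks too narrow. It needs the outcome variance to be halved, and baseline adjustment at a correlation of 0.5 removes only a quarter of it.

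What is at stake is the reader's expectation of what the trial can show. A half-width of ±0.26 sd is smaller than the 0.3 sd effect the trial is planned around, so an observed difference of that size would appear to exclude zero. A half-width of ±0.32 sd or more is larger than that effect, and the same observed difference would not exclude zero.

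**Working it through.** **Inputs.** From 2.10: n = 40 per arm; two-sided 90% interval, z = 1.645; correlation at most 0.5; sds of 1.9 points (HbA1C), 19.9 mmHg (systolic blood pressure) and 20 mg/dL (LDL). From 2.11: the contrast at 6 months, adjusted for baseline.

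**Formula.** Half-width = 1.645 × √(2v/n), in sd units, where v is the variance factor of the quantity being compared.

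**Reproducing the plan's figure.** ±0.26 at n = 40 needs v = (0.26/1.645)² × 40/2 = 0.50. At least three quantities give this half-width:

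- The mean of one arm alone: 1.645/√40 = 0.260.
- A between-arm difference in the average of two visits that are uncorrelated: v = 0.50, giving 0.260.
- A baseline-adjusted difference in the two-visit average with every pairwise correlation equal to 0.5: v = (1 + 0.5)/2 − 0.5² = 0.50, giving 0.260.

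None of these is the between-arm difference at 6 months.

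**The contrast to be reported.** For a baseline-adjusted difference at one visit, v = 1 − r², where r is the baseline-to-6-month correlation. Here the stated cap on the correlation is the favourable end, because a smaller r gives a wider interval. If AR(1) with ρ = 0.5 is extended back to baseline, r = 0.5² = 0.25.

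| r | v | Half-width, 40 per arm | Half-width, 50 per arm |
|---|---|---|---|
| 0.5 | 0.75 | 0.319 | 0.285 |
| 0.25 | 0.9375 | 0.356 | 0.319 |
| 0 | 1 | 0.368 | 0.329 |

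With t quantiles the 40-per-arm values become 0.322, 0.361 and 0.372. A simulation of the joint model with one common baseline slope gave 0.320 (all correlations 0.5) and 0.364 (AR(1) over three visits). The 3-month value therefore does not rescue the 6-month contrast.

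Relative to 0.26, the 40-per-arm values are wider by about 23% (0.319/0.26), 37% (0.356/0.26) and 41% (0.368/0.26).

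**What ±0.26 would require at 6 months.** With 40 per arm, r = √(1 − 0.50) ≈ 0.71. Otherwise n = 2v × (1.645/0.26)², which is 61 per arm at r = 0.5, 76 at r = 0.25 and 81 at r = 0.

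**Raw units at 40 per arm (r from 0.5 to 0).**

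| Outcome | Implied by ±0.26 sd | 6-month contrast |
|---|---|---|
| HbA1C, points | ±0.49 | ±0.61 to ±0.70 |
| Systolic blood pressure, mmHg | ±5.2 | ±6.3 to ±7.3 |
| LDL, mg/dL | ±5.2 | ±6.4 to ±7.4 |

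**Consistency with the power claim.** 80% power at 0.3 sd with two-sided α = 0.10 needs a standard error of 0.3/(1.645 + 0.842) = 0.121, hence a half-width of 1.645 × 0.121 ≈ 0.198. Conversely, the standard error behind ±0.26 is 0.26/1.645 = 0.158, which gives about 60% power at 0.3 sd. The two statements are made for the same n and cannot both hold.

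**The case against.** The best defence is that the sentence decides nothing. It does not set the sample size, the model, the endpoint or a decision rule, and the reported interval will come from the data. The power claim does fix the sample size, so its own inconsistency matters more. All of this stands, and it limits the weight of the point. It does not make the figure right.

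A second defence is that 50 per arm are randomized. The plan ties ±0.26 to 40 per arm, however, and with all 50 observed the half-width still exceeds 0.26, by about 10% (0.285/0.26) to 27% (0.329/0.26).

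A third is that the cap of 0.5 may be meant only for the two follow-up measurements. The baseline-to-6-month correlation would then be unstated, and ±0.26 would rest on an undeclared value near 0.71.

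Three stronger readings are tempting and are not supported:

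- A reader might infer that ±0.26 is the precision of a 3- and 6-month average. The plan does not say so, and the simpler one-arm expression gives the same number.
- A reader might take ±0.32 to ±0.36 sd as the true range. The correlation is described only as no larger than 0.5, and the text does not say that AR(1) reaches back to baseline, so ±0.36 is not an upper limit.
- A reader might infer that the later grant application will rest on this planned figure. The Discussion says that it will use the results obtained after the study is completed.

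**Conclusion.** The ±0.26 sd figure is wrong as written for the difference that the analysis will report. At 40 analysed per arm, the baseline-adjusted 6-month half-width lies between about ±0.32 sd and ±0.37 sd, depending on where the baseline-to-6-month correlation falls between 0.5 and 0. No value in that range gives ±0.26.

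The conclusion assumes complete data on 40 per arm, the outcome sd as the unit, and that the stated cap covers the pair formed by baseline and 6 months. If the sd were instead a residual sd after adjustment, the factor would be v = 1 and the half-width ±0.368 sd.

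The origin of 0.26 cannot be settled from the document. The error overstates the planned precision. It does not affect the validity of the planned analysis. It should be corrected, alongside the power statement with which it conflicts.

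**What to change.** In 2.10, replace ±0.26 sd with about ±0.32 to ±0.37 sd at 40 analysed per arm. State that this refers to the baseline-adjusted difference at 6 months, name the baseline-to-6-month correlation assumed, and add the raw-unit half-widths tabulated above. Derive the precision and power statements from the same standard error so that they agree.

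Keeping ±0.26 and labelling it as an average over 3 and 6 months is not a sound alternative. With AR(1) at 0.5 across all three visits, the baseline-adjusted average has v = 0.75 − 0.375² = 0.609 and a half-width of ±0.287 sd, and 2.11 does not report that average.

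The change to the precision statement is one sentence, with no change to design or analysis. Its only downside is that the stated precision becomes less favourable.
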